### Sample size calculation

A sample of 99 women (33 per arm) yields 90% power, 0.025 alpha to show a difference in the mean daily breast milk volume of 150 mL/day (200 mL/day standard deviation) between each of the intervention arms and control arm, allowing for 10% loss to follow-up. This includes adjustment for a 0.6 correlation between breast milk volume at study entry and breast milk volume on Day 7 at the end of the intervention phase.

### Data management

Data entry and study management will be using a purpose-built REDCap database and hosted on secure servers at SAHMRI. Electronic case report forms will be used and stored directly in REDCap, and any paper-based case report forms will be stored in a locked office at the study site. Data are collected by trained researchers and entered directly into REDCap, no confidential data are stored on data entry machines. REDCap uses a MySQL database via a secure web interface and includes a complete suite of features to support the Health Insurance Portability and Accountability Act of 1996 compliance, including a full audit trail, user-based privileges and integration with the institutional Lightweight Directory Access Protocol server [28].

In order to adhere to international best research practice and to ensure eligibility of our study for publication in scientific journals, we plan to archive the fully deidentified sequencing datafiles in the Gene Expression Omnibus (GEO or equivalent database). The sequencing data files prepared for GEO will be free of all identifiers that would permit linkages to individual research participants and variables that could lead to deductive disclosure of the identity of individual subjects, in accordance with the NIH Statement on Sharing Research Data (2003).

### Statistical analysis methods

The primary analysis will be performed according to the treatment group to which participants were randomised (intention-to-treat principle). A secondary per-protocol analysis will also be performed for each of the primary and secondary outcomes.

The primary outcome of daily expressed breast milk volume on Day 7 post intervention will be compared between treatment groups using linear regression. The results will be expressed as a difference in means with a 95% confidence interval and two-sided *p*-value. Adjustment will be made for baseline daily expressed breast milk volume and the randomisation strata (study centre). A *p*-value of less than 0.05 will be considered to indicate statistical significance. Analysis of secondary outcomes will use log-binomial regression models for binary outcomes and linear regression models for continuous outcomes with adjustment for stratification variables and other pre- specified prognostic baseline variables. Results will be presented as relative risks and differences in means respectively, along with 95% confidence intervals. Missing data will be addressed using multiple imputation. Sensitivity analyses will also be performed using the original unimputed data.

Planned sub-group analyses of the primary and secondary breastfeeding outcomes include: (i) Plurality (singleton vs. twins); (ii) Parity (primiparous vs. multiparous); (iii) Infant gestation at birth (categorical: 23^+ 0^–29^+ 6^ vs. 30^+ 0^–31^+ 6^ vs. 32^+ 0^-33^+ 6^ weeks’ gestation and continuous); (iv) Maternal body mass index (categorical: underweight/normal weight [BMI < 25 kg/m^2^] vs. overweight/obese [BMI ≥ 25 kg/m^2^] and continuous). Effect modification by each of these factors will be assessed separately by including interaction effects with treatment group in the statistical models.

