### Study population

Mothers of preterm infants born at less than 34 weeks’ gestation who intend to provide breast milk for their infant, and are within 72 h of giving birth.

The inclusion criteria will include women, 18 years or older, who have delivered a preterm infant born at less than 34 weeks’ gestation (up to 33 + 6), are between 0 and 72 h of birth, intend to provide breast milk to their preterm infant for any desired duration, and able to give informed consent. Women with a contraindication to breastfeeding such as infection with human immunodeficiency virus (HIV), as well as those with higher order pregnancies (triplet or more) will be excluded from the study.

Information on the study will be provided to eligible participants by their nurse or midwife who will ask them to complete a Consent to Contact form, and following this consent will be contacted by a study researcher (Fig. 1). After confirmation of eligibility and receipt of voluntary informed consent, women will be assigned randomly to one of three groups: brewer’s yeast, beta-glucan, or placebo in a 1:1:1 ratio using randomly permuted blocks of varying sizes. Block sizes will not be disclosed to ensure allocation concealment. Participants will be randomised using the REDCap Randomisation Module, and the randomisation schedule will be prepared using ralloc. ado in Stata by an independent statistician that is not involved with trial participants or data. The randomisation schedule will be stratified according to study site. Participants and their care providers, outcome assessors, trial investigators and data analysts will be blinded to randomisation group. Women will be allocated a random, unique, re-identifiable randomisation identification number (ID) and assigned to one of three treatment groups and be issued with study medications identified by colour. To facilitate blinding, two colours will be used for each treatment group, with six colours used in total (i.e. green, yellow, red, blue, purple, orange).

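### The primary model adjusts only for baseline volume and site, although women enter 0 to 72 h after birth; adding hours since birth and recorded prognostic factors is a cheap gain in precision

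*Protocol article*

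**What the plan says.** All references are to the Protocol article.

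- **Primary model** (Statistical analysis methods): linear regression of Day 7 daily expressed volume. "Adjustment will be made for baseline daily expressed breast milk volume and the randomisation strata (study centre"). No other covariate is named.
- **Secondary outcomes** (same section): models "with adjustment for stratification variables and other pre- specified prognostic baseline variables". Plurality, parity, gestation and maternal BMI appear by name only as subgroup factors.
- **Entry and randomisation** (Study population): eligible women "are between 0 and 72 h of birth". "The randomisation schedule will be stratified according to study site".
- **Timing of the endpoint** (Intervention; Table 2): treatment lasts seven days from enrolment, and the Day 7 visit is counted from enrolment, not from birth.
- **Sample size** (Sample size calculation): "A sample of 99 women (33 per arm) yields 90% power, 0.025 alpha" for a "difference in the mean daily breast milk volume of 150 mL/day (200 mL/day standard deviation"), "allowing for 10% loss to follow-up". On the baseline covariate the section then adds: "This includes adjustment for a 0.6 correlation between breast milk volume at study entry and breast milk volume on Day 7".
- **Data already collected** (Table 4): parity, length of gestation and plurality come from the case notes. Time since birth has to be known to confirm eligibility.

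**The concern.** Baseline volume is the only precision covariate besides site, and the sample size leans on it. Two women with the same eventual supply can have quite different entry volumes if one is enrolled at 10 h and the other at 70 h. A woman randomised within 24 h of birth cannot have a full 24-hour total before randomisation. Baseline volume is thus a mixture of elapsed time and supply, and the stated model has no term that separates them. The endpoint has a similar, smaller spread: seven days after an entry at 0 to 3 days is postpartum day 7 to 10.

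The outcome that carries the power claim also has a leaner stated covariate set than the secondary outcomes. Precision is at stake, and under one reading of the 0.6 so is part of the stated 90% power. Validity is not.

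**Working it through.** **1. Reproduce the plan's figure.** Inputs from Sample size calculation: difference 150, SD 200, correlation 0.6, alpha 0.025, power 90%, loss 10%.

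- Residual SD = 200 × √(1 − 0.6²) = 160.
- n per arm = 2 × (2.241 + 1.282)² × 160² / 150² = 28.2, so 29.
- 29 / 0.9 = 32.2, so 33 per arm and 99 in total. This matches.
- With no baseline adjustment: 2 × (2.241 + 1.282)² × 200² / 150² = 44.1, so 45, and 45 / 0.9 = 50 per arm.
- Two-sided 0.05 (or one-sided 0.025) gives 24, inflated to 27, which does not match.

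The plan therefore used two-sided 0.025 with baseline volume as the single covariate. That alpha is used below.

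**2. Power of the planned model if 0.6 is the plain correlation.** Evaluable n = 33 × 0.9 = 29.7 per arm. Noncentrality = 150 / (200 × √(1 − R²) × √(2/29.7)), noncentral t with 2n − 2 degrees of freedom.

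- R² = 0: power 72.1%.
- R² = 0.36: power 90.2% (the normal approximation gives 91.5%).

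The planned model keeps the whole 36% reduction in variance.

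**3. What further covariates would add on that reading.** The article gives no figure, so the share q of residual variance explained is an assumption. Residual SD = 160 × √(1 − q).

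| q | Residual SD | Power | Gain (points) |
|---|---|---|---|
| 0 | 160.0 | 90.2% | – |
| 5% | 155.9 | 91.7% | 1.5 |
| 10% | 151.8 | 93.1% | 2.9 |
| 20% | 143.1 | 95.6% | 5.5 (before rounding) |

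**4. If 0.6 held only at a fixed postpartum hour.** In a linear model where hours since birth are unrelated to Day 7 volume, let b = corr(baseline volume, hours). The raw baseline then has R² = 0.36 × (1 − b²), so the share of the gain lost is b².

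| b | R² | Power, hours not in model |
|---|---|---|
| 0.3 | 0.328 | 88.6% |
| 0.5 | 0.270 | 85.7% |
| 0.7 | 0.184 | 81.2% |
| 0.8 | 0.130 | 78.5% |

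In this linear setting, losing more than half of the gain needs b above √0.5 = 0.71, which is a plain correlation below 0.6 × 0.71 = 0.42.

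**5. The same reading with multiplicative growth.** One fully specified example, simulated with 400,000 women, all parameters assumed: entry h uniform over 0 to 72 h; supply u standard normal; standardised Day 7 volume = 0.6u + 0.8e, with e standard normal; baseline = 300 × exp(0.5u) / (1 + exp(−(h − 48)/14)).

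| Covariates | R² | Power |
|---|---|---|
| Raw baseline | 0.09 | 76% |
| log(1+baseline) alone | 0.07 | 76% |
| Raw baseline + hours | 0.20 | 82% |
| log(1+baseline) + hours | 0.32 | 88% |

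Across a range of assumed rise curves, power was about 75 to 83% for raw baseline, 78 to 86% with hours added, and 84 to 90% with log(1+baseline) plus hours. A separate set with entry confined to 36 to 72 h gave 79 to 85% for raw baseline. Much of the improvement needs the log form and hours together; neither alone delivers it.

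**The case against.** Adjusting for the baseline value of the outcome and the stratification factor is a standard, pre-specified choice. Randomisation protects the comparison whatever else is left out. The sample size needs no further covariate, and naming a factor for subgroups does not oblige its use as a main effect. All of this stands.

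A reader might go further and infer that the omission discards most of the precision baseline volume was meant to bring, so that true power is near 76% rather than 90%. The article does not support that. Sample size calculation states the 0.6 as the correlation between volume at study entry and volume on Day 7, which is the plain correlation with the covariate that is in the model. The low-power figures appear only if 0.6 is reinterpreted as holding at a fixed hour, with an assumed entry pattern and an assumed rise in volume. The article itself gives reasons for caution about both. Its Background cites delayed secretory activation in 82% of women in one preterm cohort, which makes a steep rise inside 72 h less certain. The consent pathway (staff information, consent to contact, researcher contact, consent) makes entry spread evenly from hour 0 doubtful.

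Two further limits also stand. An additive hours term adjusts for average differences; it does not remove the spread of postpartum day 7 to 10. An analysis plan, not shown here, may already refine the form of the baseline covariate or add adjusted analyses.

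What remains is that the article states a specific primary adjustment set, and that set omits a known, freely available source of variation.

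**Conclusion.** The point holds as a cheap improvement, of minor to moderate severity. No bias arises.

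- Taking the 0.6 as worded, the planned model delivers about 90% power. The omission forgoes about 1.5 to 5.5 power points if added covariates explain 5 to 20% of residual variance (an assumed range).
- If the 0.6 applies only at a fixed postpartum hour, raw baseline volume may lose much of the planned gain: power about 75 to 83% in the main assumed scenarios, against about 84 to 90% with log(1+baseline) plus hours.

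The article gives no source for the 0.6, no distribution of entry times and no correlation of baseline volume with hours since birth. The size of any loss therefore cannot be determined from it. The recommendation does not depend on which reading is right: the fuller model adds precision under the first and protects power under the second.

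**What to change.** Before unblinding, pre-specify the primary model as Day 7 volume on treatment, site, baseline volume (as log(1+x) or another flexible form), hours from birth to randomisation, gestation at birth (continuous), plurality and parity. Keep the model with baseline volume and site only as a sensitivity analysis. If the analysis plan already does this, only the wording needs aligning.

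Cost: a sentence in the analysis plan and no new data, since every variable is already recorded or needed for eligibility. The four added terms (hours, gestation, plurality, parity) use about four degrees of freedom, with about 90 completers expected (99 × 0.9 = 89.1). The choice has to be fixed in advance, because covariates selected after unblinding would be open to challenge.

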### Objectives

This main objective of this study is to determine whether in mothers of a preterm infant born at less than 34 weeks’ gestation, does taking brewer’s yeast or beta-glucan compared with placebo lead to an increase daily expressed breast milk volume after seven days.

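### The trial is sized at alpha 0.025 for each of two active-versus-placebo comparisons but analysed at p<0.05 with 95% intervals, so the family-wise error is about 9%, not 5%

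*Protocol article*

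**What the plan says.** Three places in the protocol article bear on this.

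- **Objectives.** There is one main question with two routes to a positive answer: "does taking brewer’s yeast or beta-glucan compared with placebo lead to an increase" in daily expressed volume after seven days.
- **Sample size calculation.** "A sample of 99 women (33 per arm) yields 90% power, 0.025 alpha" for a 150 mL/day difference (SD 200 mL/day) "between each of the intervention arms and control arm". The calculation allows for 10% loss to follow-up and a 0.6 correlation between baseline and Day 7 volume. It does not say whether 0.025 is one-sided or two-sided, or why it was chosen.
- **Statistical analysis methods.** Day 7 volume is compared by linear regression adjusted for baseline volume and study centre. "The results will be expressed as a difference in means with a 95% confidence interval" and a two-sided p-value. A p-value "of less than 0.05 will be considered to indicate statistical significance". This sentence comes straight after the primary model and before the secondary outcomes, so it governs the primary test.

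No section names a multiplicity adjustment, a preliminary global test or a testing order for the two comparisons. No interim analysis is planned, so no alpha is spent elsewhere.

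**The concern.** The design and the analysis appear to use different significance levels for the same two tests. An alpha of 0.025 for each of two comparisons is what a Bonferroni split of 0.05 looks like. If the analysis then judges each comparison at 0.05, the split is lost.

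The two tests form one family. They share a placebo arm, the products come from the same yeast species, and the objective is met if either one works. Two things are at stake:

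- the chance that the trial reports an effect of at least one product when neither has any;
- an unambiguous primary conclusion. A p-value between 0.025 and 0.05 would count as significant under the analysis section and not under the design, which leaves the choice open after the data are seen.

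**Working it through.** **Inputs (protocol article).** Difference 150 mL/day, SD 200 mL/day, baseline correlation 0.6, power 90%, alpha 0.025, loss 10%, two comparisons with control (Sample size calculation); allocation 1:1:1 (Study design and setting); two-sided p<0.05 and 95% CI (Statistical analysis methods).

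**Step 1: reproduce 33 per arm.** Adjusting for baseline by regression multiplies the variance by 1 − 0.6² = 0.64, so the adjusted SD is 200 × √0.64 = 160.

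n per arm = 2(z₁₋α/₂ + z₀.₉₀)² × 200² × 0.64 / 150², with z₀.₉₀ = 1.2816.

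| Alpha | z | n evaluable | After 10% loss (÷ 0.9) | Total |
|---|---|---|---|---|
| Two-sided 0.025 | 2.2414 | 28.24 → 29 | 32.2 → 33 | 99 |
| Two-sided 0.05 (= one-sided 0.025) | 1.9600 | 23.91 → 24 | 26.7 → 27 | 81 |

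The first row matches the plan exactly. The second falls 18 women short. A t-based calculation at two-sided 0.025 gives 30, or 34 after loss, close to the plan. Leaving out the baseline adjustment gives 45, or 50 after loss, which does not fit.

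**Step 2: family-wise error under each rule.** With equal arms and a shared control, the two test statistics have correlation 0.5. With both nulls true, the probability of at least one rejection is 1 − P(|Z₁| < c and |Z₂| < c) under a bivariate normal with that correlation.

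| Rule per comparison | c | At least one two-sided rejection | At least one false benefit only |
|---|---|---|---|
| Two-sided 0.05 | 1.960 | 9.1% | 4.5% |
| Two-sided 0.025 | 2.241 | 4.6% | 2.3% |

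The ratio is about 1.95 in both columns (9.07/4.65 and 4.54/2.32). Treating the tests as independent gives upper comparisons of 1 − 0.95² = 9.75% and 1 − 0.975² = 4.9%. A Dunnett critical value (large-sample) is 2.212, a nominal two-sided level of about 0.027 per comparison.

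If yeast versus beta-glucan were also tested at 0.05, simulation of all three pairwise tests gives 12.2%. That is conditional: the plan does not commit to this test.

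**Step 3: power under each rule.** Evaluable women per arm: 33 × 0.9 = 29.7.

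| Method | At two-sided 0.025 | At two-sided 0.05 |
|---|---|---|
| Normal approximation | 91.5% | 95.1% |
| t-based, degrees of freedom pooled over three arms | 90.6% | 94.6% |

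The quoted 90% belongs to the 0.025 rule.

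**The case against.** **The 0.025 could be one-sided.** It would then equal the two-sided 0.05 of the analysis, and the two sections would agree. The sample size text gives no sidedness and does not name the method of baseline adjustment. With a change-score variance factor of 2(1 − 0.6) = 0.8, two-sided 0.05 gives 29.9 → 30, and 30 × 1.10 = 33. So 33 alone does not prove a two-sided 0.025. But this route needs an analysis the plan does not use, since it adjusts for baseline by regression. It also needs loss to be handled by multiplying by 1.10; dividing 30 by 0.9 gives 33.3 → 34. The reading that follows the plan's own model fits without either step.

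**The p-value might be multiplicity-adjusted.** A Bonferroni-adjusted p<0.05 is the same as a raw p<0.025. But the plan does not say this, and it pairs the p-value with a 95% interval, which would not match.

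**The 9.1% includes false findings of harm.** This is correct. The risk of wrongly endorsing at least one product is 4.5%, and 9.1% should not be read as that risk. But the plan states two-sided tests, and the near-doubling relative to the design holds on either count.

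**Separate products need no adjustment, or the SAP will decide.** The first is a defensible position in general, but it is not the one the sample size takes. As to the SAP, the article does not merely stay silent: it fixes a threshold that conflicts with its own design alpha. An SAP using either level would contradict one of the two sections.

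**Conclusion.** The concern holds. The two sections set different significance levels for the same primary comparisons, and the analysis rule as written does not keep the error control that the sample size was built on. Family-wise two-sided error is 9.1%, against 4.6% at the design alpha. The corresponding risk of at least one false finding of benefit is 4.5% against 2.3%.

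These rates assume that both nulls are true, the arms are equal, the placebo group is shared and the test statistics are approximately normal. That 0.025 is a halved two-sided 0.05 is an inference from the arithmetic under the planned regression. It is strong but not stated in the text. Because the rule decides the primary conclusion, it should be corrected before unblinding.

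**What to change.** In Statistical analysis methods (and the SAP), replace the plain p<0.05 rule for the primary outcome. Either:

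- test each of the two active-versus-placebo contrasts at two-sided 0.025 and report 97.5% confidence intervals; or
- name Holm or Dunnett with family-wise two-sided error of 0.05, and state how the reported intervals correspond to it.

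In Sample size calculation, say that 0.025 is two-sided and is 0.05 divided over two comparisons. If yeast versus beta-glucan is reported, label it exploratory.

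The cost is a sentence or two. No extra participants are needed, because 33 per arm was already computed at this level and power per comparison stays at the stated 90%. What is given up is the roughly 95% power that the looser rule would have had.

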### Data monitoring and safety

The trial coordinating centre (SAHMRI) will perform ongoing monitoring via weekly reports of participants screened/enrolled/randomised, visits due/overdue/missed, adverse and serious adverse events, product inventory and dispense records, sample collection logs, and participant communication logs. The weekly reports will be reviewed at weekly trial management meetings. No interim analyses are planned.

An individual participant may only be unblinded in emergency situations, where the Investigator decides a participant cannot be adequately treated without knowing the identity of their treatment allocation. To break the randomisation code the Principal Investigator must contact the randomisation facility/personnel. The time, date, participant study ID and reason for unblinding will be documented. Events leading to the emergency breaking will be recorded in the serious adverse event (SAE) report form.

### Ethical issues and dissemination

The BLOOM study will be conducted in accordance with the approved version of the Study Protocol and in compliance with the Australian National Statement on Ethical Conduct in Research Involving Humans which builds on the ethical codes of the Declaration of Helsinki and the Principles of International Conference on Harmonisation Good Clinical Practice (as adopted in Australia). All study materials and study protocol (current version 1.1) have been reviewed and approved by the Women’s and Children’s Health Network Human Research Ethics Committee (HREC), South Australia (HREC/22/WCHN/00001), as well as the research governance officers at each of the study sites. Any change to the protocol or Informed Consent Form that affects the scientific intent, study design, patient safety or may affect a participant’s willingness to continue participation in the study is considered an amendment, and therefore, will be written and filed as an amendment to this protocol and/ or informed consent form. All such amendments will be submitted to the HREC, for approval prior to becoming effective.

The primary and key secondary breastfeeding objectives will be analysed and reported first. Study findings will be submitted for peer-reviewed publication and for presentation at appropriate local and international conferences. In addition, study findings will be disseminated to participants through a brief lay summary. No participants will be identified in the dissemination of study results and data collected will be treated with confidence.

